### Randomization and blinding

2.4

The staff member will refer to a specific random number handbook generated by an independent statistician based on statistical software before study activation to determine the study intervention assigned to the randomized patient. The randomization schedule is layered by the position of each 4-bit variable block. Participants will be randomly assigned to 1 of the 2 groups in a 1:1 ratio after completion of baseline assessment, according to a randomized block list generated by an independent research assistant using R, and the code will be kept in opaque sequentially numbered envelopes. The treatment allocation codes will be enclosed by an independent research assistant in sequentially numbered opaque envelopes and will not be revealed until the participants have completed all baseline assessments and immediately before the first massage treatment. The single-blind method is adopted in this study, and there are two-level blind methods. First, blind evaluation, in which the participants are evaluated by a third party who does not know the grouping. Second, the blind statistical analysis, where the statistical data will be analyzed by statisticians with unclear grouping and its meaning. (Fig. 1)

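### Section 2.4 gives two incompatible allocation procedures and an unclear block scheme, so allocation concealment cannot be relied on as written

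*Protocol article*

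**What the plan says.** All of this is in the protocol article, section 2.4 (Randomization and blinding), unless another place is named.

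- **First account.** "The staff member will refer to a specific random number handbook generated by an independent statistician", prepared before study activation, "to determine the study intervention assigned to the randomized patient".
- **Second account.** Children are "randomly assigned to 1 of the 2 groups in a 1:1 ratio after completion of baseline assessment". The arm is found "according to a randomized block list generated by an independent research assistant using R". As for concealment, "the code will be kept in opaque sequentially numbered envelopes". Their contents "will not be revealed until the participants have completed all baseline assessments and immediately before the first massage treatment".
- **Blocking.** "The randomization schedule is layered by the position of each 4-bit variable block".
- **Blinding.** "The single-blind method is adopted in this study, and there are two-level blind methods". The two levels are the outcome assessor and the statistician. Treating staff and families are not listed as blinded.
- **Control arm.** The Abstract and section 2.5 give the control group basic rehabilitation only, with no sham massage.
- **Centres, size and status.** There are four centres (section 2.1) and 182 children (section 2.2.1). Recruitment began on June 1, 2019 and was continuing when the article was written (section 4).

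**The concern.** The two accounts cannot both be followed literally. If a staff member learns the arm from the handbook, the envelope adds nothing. If the envelope gives the arm, staff have no reason to consult the handbook. The stated generator also changes, from a statistician to a research assistant.

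Allocation concealment is at stake. Someone who knows or can guess the next arm can influence which child is enrolled, or when. The criteria leave room for this: inclusion criterion 5 in section 2.3 (that the family follows the doctor's advice during the study) is a matter of judgement. Blinded assessment and the intention-to-treat analysis in section 2.12 both act after randomisation and cannot undo selection that came before it. The Discussion also relies on rigorous randomisation to balance the types of spastic cerebral palsy between groups.

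The block wording adds a second, separate route to the same problem. Past assignments can be observed because massage is given five days a week for 12 weeks in one arm and not in the other. With short blocks of known length, past assignments predict later ones.

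**Working it through.** **Step 1. The two accounts side by side**

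| | First account | Second account |
|---|---|---|
| Who generates the sequence | independent statistician | independent research assistant |
| What holds it | random number handbook | block list, codes in opaque numbered envelopes |
| What tells staff the arm | looking in the handbook | the envelope, after baseline and just before first treatment |

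The section does not say that one is the source of the other. It does not say who the staff member is, where the handbook is kept, or whether later entries can be seen.

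**Step 2. How predictable blocked allocation would be**

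The article states no figure for this, so there is none to reproduce. The inputs are the 1:1 ratio (section 2.4) and an assumed fixed block length. It is also assumed that the guesser knows every earlier assignment in the same list.

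For blocks of 4 there are 6 possible sequences, hence 6 × 4 = 24 positions.

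- *Certain assignments.* AABB and BBAA each have 2 positions fixed by what came before. ABAB, ABBA, BABA and BAAB each have 1. Total 2 × 2 + 4 × 1 = 8, and 8/24 = 33.3%.
- *Best guess (name the arm with more places left).* The chance of being right at positions 1 to 4 is 1/2, 2/3, 2/3 and 1. The sum is 17/6 per block, so 17/24 = 70.8%, against 50% with no information.

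For a block of length 2m, the certain share is 1/(m + 1). The expected number of correct guesses is m + (4^m / C(2m, m) − 1)/2.

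| Assumed fixed length | Certain in advance | Best guess right |
|---|---|---|
| 4 (m = 2) | 1/3 = 33.3% | [2 + (16/6 − 1)/2]/4 = 70.8% |
| 6 (m = 3) | 1/4 = 25.0% | [3 + (64/20 − 1)/2]/6 = 68.3% |
| 8 (m = 4) | 1/5 = 20.0% | [4 + (256/70 − 1)/2]/8 = 66.6% |

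**Step 3. Scale**

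In one list, 182 children make 45 complete blocks of 4 with 2 children over. The expected number of certain assignments is 45 × 4/3 = 60 (simple proportion: 182/3 = 60.7). At length 6 the proportion gives 182/4 = 45.5, and at length 8 it gives 182/5 = 36.4.

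These are upper figures. They apply within a centre if each centre has its own list. If one list serves all four centres, a recruiter sees only part of the history and predictability is lower. The block sentence does not make clear which arrangement applies.

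**The case against.** The best defence is that the accounts can be joined: the handbook is the master schedule and the envelopes are how it is released. Section 2.4 does state opaque, sequentially numbered envelopes and disclosure only after baseline. It does not place the handbook with recruiters. Custody of the list is the kind of detail that a condensed article leaves to the full protocol. The block phrase looks like a translation problem, and its word for variability may mean that lengths already vary.

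Much of this stands, and it rules out three stronger readings that a reader might infer.

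- *That the trial is open-label.* The article calls it single-blind, with assessor and statistician blinded. What can be said is that therapists and families are in effect unblinded, because the control arm has no sham.
- *That coming assignments are visible, hence fully predictable.* Nothing says that recruiting staff hold the handbook or can see later entries, and the envelope procedure points the other way.
- *That blocks are fixed at 4 and this is now public.* That is one reading of an unclear phrase. Even on that reading, two thirds of assignments are not certain in advance.

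What the defence does not remove is the conflict in the text. The master-schedule reading is not stated, it leaves two different generators, and it does not fit an instruction that staff determine the arm by consulting the handbook. That is a contradiction in a rule the article gives, not a detail left out of it.

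**Conclusion.** The point holds in a limited form. Section 2.4 states two unreconciled allocation procedures with different generators, and a block scheme that cannot be read with confidence. Followed literally, the first procedure bypasses the concealment that the second provides.

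The consequences are conditional. Concealment fails if staff involved in recruitment use the handbook. Separately, if blocks are fixed at 4 and earlier assignments in the same list are known, 33.3% of assignments are certain and 70.8% can be guessed. The range down to blocks of 8 is 20.0% and 66.6%, and less if one list covers all four centres. The article does not show that either condition is met. This is a correction worth making because it is cheap and protects the comparison; it is not evidence that selection has occurred.

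**What to change.** Rewrite section 2.4 around one procedure:

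1. Name one generator, the independent statistician.
2. Remove the instruction that staff find the arm in the handbook, and keep the list away from anyone who recruits.
3. Release each assignment only by opening the next numbered opaque envelope, after consent and baseline assessment are recorded.
4. Replace the block sentence with a clear one that says what the list is stratified by and whether block sizes vary. If sizes already vary at random and are withheld from sites, correct the wording only. If not, use randomly mixed sizes, for example 4, 6 and 8, for children still to be randomised, and do not give them in site documents.

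Mixed sizes leave few or no assignments certain, but they do not bring guessing down to 50%. Someone who knows the full history can still name the arm that is behind. With equal numbers of blocks of 4, 6 and 8, the expected correct share is (2.83 + 4.10 + 5.33)/18 = 68.1%. Restricting access to the list and to the allocation history therefore matters as well.

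The cost is a short amendment, new envelopes for the remaining children and slightly looser running balance. Children already randomised are not affected, and the article does not say how many remain.

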**Figure 1 F1:**
[figure not shown]
Flow diagram of the study design.

### Treatment protocol

2.5

1. Experimental group

1) Pediatric massage method:^[18]^

Place the child in a quiet, warm treatment room at room temperature between 25°C and 28°C. Appease the child before the operation to keep him in a quiet state.

Steps:②

Stimulation Governor Vessel and The Bladder Meridian of Foot-Taiyang. The child will take the prone position, the doctor will stand on the right side, and will use the Mofa along Governor Vessel direction to rub the entire spine, from top to bottom 3 to 5 times; Anrou the back of the first sideline and the second sideline of The Bladder Meridian of Foot-Taiyang by up to down 3 to 5 times; pinch the spine from top to bottom 3- 5 times; rubbing Shenshu (BL23), Mingmen (DU4), and Baliao.②

According to the principle of spinal neuroanatomy, the projection point on the surface of the spinal nerve root of children with spastic cerebral palsy will be determined, which will usually be the place with a cord or nodal reactants or the position of muscle tension and spasm, and the stimulation will be performed by rubbing for 3 min.③

Local treatment: According to the degree of spasm of the paralyzed limb, local treatment will be carried out using the traditional methods. The child will be placed in a supine position, and the doctor will use rolling to relax limbs, simultaneously, by the passive movement of the corresponding joint. Pressing will be performed to knead paralytic limb in turn, from top to bottom, applying gentle holding method to paralytic limb for 3–5 times. Following this, moderate shaking, pulling, or pulling to the corresponding joints of the paralyzed limb will be applied.④

Regulating yin and yang. The child will be placed in the supine position; the doctor will stand on the head side, opening the Tianmen 30 times, separate-pushing the Kangong 30 times, separate-pushing Ying Xiang (LI20) 30 times, kneading Taiyang (EX-HN5) for 1 min, and grasping Jianjing (GB21) 3 to 5 times. (Fig. 2)

(1)Basic rehabilitation treatment group(2)Treatment Procedure: 1 treatment per day, 5 times a week, 15 to 20 minutes each time, 4 weeks for a course of treatment, a total of 3 courses of treatment. To ensure the scientific and accurate results of the assessment, the assessment will be performed in a single-blinded manner, and all evaluations will be performed by a trained tutor.

**Figure 2 F2:**
[figure not shown]
Location of acupoints.

(1)Quality assurance of massage treatment(2)All operators conduct unified training and consistency check. Kappa value is greater than 0.8 to perform the above-mentioned massage operation independently.(3)Control group: basic rehabilitation treatment group

Basic rehabilitation treatment: All children will receive basic treatment according to the rehabilitation concept applied in the individual hospital and/or as demanded by the cost bearers. It will consist of physical factor therapy, occupational therapy, physiotherapy, and medical exercise.

### Measures

2.6

#### Outcome assessment

2.6.1

All the outcomes will be measured before enrollment, at the end of 4 weeks, the end of 8 weeks, and the end of 12 weeks follow-up. The summer of all the measures in the trial is shown in Figure 3. (Fig. 3)

**Figure 3 F3:**
[figure not shown]
Trial process chart.

### Primary outcome measure

2.7

1.Modified Ashworth ScaleOwing to the presence of sputum, quadriplegia, and hemiplegia, the lower limb muscle tone (triceps, soleus, gastrocnemius) will be assessed using a modified Ashworth scale.^[19,20]^ It includes 6 rating levels, 0, 1, 1+, 2, 3, and 4. For statistical convenience, 0, 1, 1+, 2, 3, and 4 levels of the muscle tension level in the scale will be determined to be 1, 2, 3, 4, 5, and 6 points, respectively. All subjects are guaranteed not to be treated with any muscle relaxants. During the evaluation, efforts should be made to avoid position metastasis, skin irritation, low ambient temperature, emotional agitation, pain, urinary tract infection, or urination before the examination. If there is a clonic or transient paroxysmal contraction, test again after the disappearance.2.Gross motor function rating scale (GMFM)

The gross motor function score will be evaluated using the GMFM for gross motor function evaluation. GMFM currently has 88 versions (GMFM-88) and 66 items (GMFM-66).^[21]^ GMFM-88 is a sequential scale, each using a 4-level scoring method, divided into 5 functional areas: Area A (lying position and turning over), a total of 51 points (17 items); Area B (sitting), total score 60 points (20 items); Area C (crawling and squatting), total score of 42 points (14 items); Area D (station), total score 39 points (13 items); Area E (walking, running and jumping). The total score is 72 points (24 items). The evaluation results include 5 functional distinction values and total scores expressing the corresponding energy regions and overall gross exercise capacity, respectively. The Chinese translation is based on the 1993 GMFM revision. Evaluate 3 designated physicians or therapists to perform in a quiet, independent, well-lit room. The room temperature will be controlled at 20°C to 30°C, and the children's clothes will be 1 to 2 layered. In the absence of a violation of the assessment requirements, the same family members should be present in each assessment to encourage the child to perform at an optimal level.

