**Methods/Design::**

The study will be a multicenter, single-blinded, randomized-controlled pilot trial. During the period from June 2019 to December 2020, 182 children with spastic cerebral palsy will be randomly divided into experimental and control groups in a 1:1 ratio. The experimental group will undergo the modified selective spinal massage method combined with the basic rehabilitation treatment, while only the basic rehabilitation treatment would be performed for the control group. The intervention period of the study will last 12 weeks, 5 days weekly on weekdays. The primary outcomes include a modified Ashworth scale assessment and gross motor function test. The secondary outcomes include the 4-diagnostic scale of Chinese medicine and children's intelligence. The observation index will be measured during the complete 12 weeks duration after the treatment of the child, that is, before treatment, after 4 weeks of treatment, after 8 weeks, and after 12 weeks of treatment.

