### Statistical analyses^[25]^

2.12

The primary analysis will be performed using intention-to-treat methods and therefore include all randomized child data. All data will be checked into the double machine using Epidata 3.1 software for database management.

Specific statistical analysis methods: The baseline characteristics of patients in the 2 groups will be reported using frequency distribution and descriptive statistics (including measurements of concentration trends and dispersion). The main analysis of the comprehensive measurement of the rate of counting data will be the chi-square test. Two independent samples of the *t*-test will be performed between the 2 groups. The paired t-test will be used to compare the outcome variables of each treatment group before and after the treatment. The difference between the multiple measurements of the same group will be conducted using the multiple measures data analysis of variance, combined with logistic regression analysis to examine the adjustment effect of clinically relevant covariates, which will be the results (gender, birth weight, gestational age). We will also follow the pre-specified subgroup analysis. All analyses will be performed using the R software. The aforementioned steps will be monitored by the third-party tests, and the quality control of the test will be carried out. The blind law is unified and responsible.

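### The between-group comparison of Ashworth points, as naturally read, is an unadjusted t-test that leaves out the baseline grade collected on every child

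*Protocol article*

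**What the plan says.** The abstract names two primary outcomes: "The primary outcomes include a modified Ashworth scale assessment and gross motor function test". Section 2.7 describes the Ashworth scale: "It includes 6 rating levels, 0, 1, 1+, 2, 3, and 4". The grades are then turned into scores, and the only reason given is convenience ("For statistical convenience, 0, 1, 1+, 2, 3, and 4 levels of the muscle tension level in the scale"). In order, they take the equally spaced values from 1 to 6.

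Section 2.12 then lists the methods.

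- **Rates, between groups:** "The main analysis of the comprehensive measurement of the rate of counting data will be the chi-square test".
- **Scores, between groups:** "Two independent samples of the *t*-test will be performed between the 2 groups". The sentence names no outcome, no time point, and neither endpoint nor change score.
- **Before against after, within each arm:** a paired t-test.
- **Repeated visits, within the same group:** analysis of variance for repeated measurements.
- **Covariates:** the methods are "combined with logistic regression analysis to examine the adjustment effect of clinically relevant covariates", listed as gender, birth weight and gestational age.

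Section 2.6.1 has all outcomes measured before enrolment and at weeks 4, 8 and 12, so each child has a baseline Ashworth grade. Section 2.3 admits muscle tone from grade I to IV, so baseline grades can vary widely.

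**The concern.** The only between-group method that fits a 1 to 6 score is the two-sample t-test. As listed, baseline enters explicitly only in within-arm comparisons, which do not estimate the treatment effect. The one adjusted model is a logistic regression, which does not suit a six-point score and does not include the baseline grade.

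A child's tone at entry is likely to be among the better predictors of tone at week 12. Leaving it out keeps between-child variation in the error term that the trial has already measured and could remove. At stake is power on a primary outcome, and precision of the effect estimate, at an unchanged sample size. The validity of the test is not at stake.

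A smaller matter is that equal steps between codes are an assumption. The step from 1 to 1+ counts as much as the step from 3 to 4, so a mean difference in points depends on the coding.

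**Working it through.** **1. The plan's own size.** Section 2.2.1 gives two-sided α = 0.05, power 0.80, a 20% absolute difference, 82 per group, and 91 after a 10% allowance. The two rates are not stated. Assuming 0.60 and 0.80 (mean 0.70):

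n = [(1.96·√(2·0.70·0.30) + 0.8416·√(0.60·0.40 + 0.80·0.20)) / 0.20]² = [(1.270 + 0.532)/0.20]² ≈ 81.2, so 82.

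82 × 1.10 = 90.2, so 91 per group and 182 in all. The figures reproduce. They concern a rate, so the Ashworth points have no power calculation of their own. I use 82 per arm below.

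**2. Closed form.** For a continuous score with baseline correlation ρ, relative to an unadjusted endpoint comparison, the variance factor is 1 − ρ² for ANCOVA and 2(1 − ρ) for a change score. The effect giving the unadjusted test 80% power at 82 per arm is (1.960 + 0.8416)·√(2/82) = 0.438 SD. With factor f, power is Φ(2.8016/√f − 1.96). For example, ANCOVA at ρ = 0.5 gives Φ(2.8016/√0.75 − 1.96) = Φ(1.275) = 89.9%.

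| ρ (assumed) | Variance removed by ANCOVA | ANCOVA power | n per arm for 80% |
|---|---|---|---|
| 0.3 | 9% | 83.6% | 75 |
| 0.5 | 25% | 89.9% | 62 |
| 0.7 | 51% | 97.5% | 42 |
| 0.8 | 64% | 99.7% | 30 |

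The last column is 82·(1 − ρ²), rounded up.

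**3. Six-grade simulation.** Baseline and outcome are cut from correlated latent normals into six assumed grades. There are 82 per arm, a latent shift of 0.4 SD, and 4,000 runs.

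| ρ (assumed) | t-test, endpoint | t-test, change | ANCOVA on 1–6 points |
|---|---|---|---|
| 0.3 | about 70% | 54% | 73% |
| 0.5 | about 70% | 67% | 80% |
| 0.7 | about 70% | 85% | 90% |
| 0.8 | about 70% | 94% | 97% |

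The gain from ANCOVA is 3, 10, 20 or 27 points over the endpoint t-test, and 19, 13, 5 or 3 points over the change-score t-test. A separate simulation of 5,000 runs, with cumulative grade proportions of 5, 20, 50, 78 and 93%, gave 69% for the endpoint t-test. ANCOVA had 78% (ρ = 0.5) and 90% (ρ = 0.7).

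**4. Spacing.** In that 5,000-run simulation, codes 1–6 and codes 0, 1, 1.5, 2, 3, 4 had nearly equal power (68.6–68.7% against 67.3–67.7%). They disagreed on significance in about 5.5% of trials at the 0.4 SD shift and in 1.5–1.8% under no effect. Null rejection was 4.9–5.5% for every method.

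**5. Ordinal model against ANCOVA.** In a smaller set of runs (300 per cell, shift 0.4), a proportional-odds model with baseline grade had 81, 88 and 94% power at ρ = 0.5, 0.7 and 0.8. ANCOVA on the points had 80, 90 and 96%. With a Monte Carlo error of about 2 points or less per figure, neither is shown to be better.

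**The case against.** **The link is inferred.** Section 2.12 does not name the Ashworth scale beside the t-test. It calls a chi-square test of a rate the main analysis, and the trial is sized on a rate. That stands. The natural reading still holds, because section 2.7 converts grades to points for analysis and no other listed between-group test takes a score.

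**The t-test may be on change scores.** Then baseline is used, and it would be wrong to say that it is wasted. That also stands, and it shrinks the gain at high correlation. ANCOVA still had the higher power at every correlation tried.

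**Model details belong in an analysis plan that is not shown.** This is fair for what an article leaves open. Here the article itself states the test and the covariate list.

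**A stronger reading: the 1–6 coding makes the primary result arbitrary, so an ordinal model is required.** A reader might infer this from the stated motive of convenience, but the material does not support it. The coding is fixed in advance, so nobody can choose it after seeing data. A t-test on increasing codes does use the order of the grades. Type I error is sound. Disagreement between codings in about 5% of trials is what valid tests show near the threshold: in another simulation at shifts of 0.3 to 0.45, the 1–6 t-test and the rank test disagreed in 3.6 to 4.6% of trials, against 4.1 to 5.2% for the two codings. The ordinal model shows no power advantage over ANCOVA.

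**One grade per child is assumed.** Section 2.7 lists several muscles without saying how they combine. If grades are summed, a six-level proportional-odds model would not apply as written.

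**Conclusion.** The point holds as a modest, optional improvement. By natural reading, the arms are compared on Ashworth points without adjustment, and the stated covariates omit the baseline grade. Adding it would raise power from about 70% to between 73% and 97% under the assumed 0.4 SD shift and correlations of 0.3 to 0.8. Against a change-score t-test the gain runs from 19 points at ρ = 0.3 down to 3 points at ρ = 0.8.

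These sizes rest on assumed grade distributions, an assumed shift and assumed correlations, none of which the article supplies. Centre was not simulated. The direction does not depend on which reading of the t-test is right.

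The planned test is valid, and nothing here supports a claim that it is biased or that equal spacing undermines the trial.

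**What to change.** In section 2.12, state that the arms will be compared on the post-treatment Ashworth score by a linear model with arm, baseline Ashworth score and centre (ANCOVA on the 1–6 codes). Report the adjusted mean difference with its 95% confidence interval, and the distribution of grades by arm so that the result can be read without relying on the codes. Say which visit is analysed.

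Optionally, add a proportional-odds model with the same terms as a sensitivity analysis, provided one grade per child is analysed. It does not depend on code spacing. In return its proportional-odds assumption needs a check, and it yields an odds ratio instead of a difference in points.

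The cost is a few lines of text and standard R code. No new data, visits or children are needed, and the sample size stays as it is.
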